# Ethics and Data Management

## Ethical and Other Approvals

Ethical clearance for this proposal has been granted by the Public Healthcare Society (PHS) Ethics Review Board in India. Ethical clearance will be sought from the London School of Hygiene and Tropical Medicine in the UK. The study protocol of the overarching study has been submitted for review by the Health Ministry Screening Committee which is given technical assistance by the Indian Council of Medical Research. Government clearance is currently being sought from the National Rural Health Mission in the State of Uttar Pradesh. Funding for the research is provided by MSD for Mothers, who have approved the study protocol.

## Ethical Considerations

The study must pose no major risk to individuals involved in the study. This is unlikely to be the case since the research requires no invasive procedures or examinations. The research activities involving data collection through the household survey are not anticipated to cause any harm. Data collection is based on standard tools that have been repeatedly implemented on different populations in numerous countries. The main cost to participants will be the time given by the interviewees. Some of the interviews with households will involve women whose baby may have recently died. The enumerators will be trained to deal with such cases sensitively. It is not anticipated that the information intervention itself will cause any harm. It will be made clear to study participants that they will be at liberty to withdraw from the study at any point without reason. Other more general ethical issues are addressed below: informed consent; processes to maintain confidentiality of the data collected (ie. secure storage of the questionnaires; anonymised data when digitised; secure storage of data including encryption), training of interviewers so that they approach the maternal health subject with sensitivity, how to handle breaches of confidentiality by members of the data collection and research teams, and appropriate dissemination of data.

## Informed Consent

Informed consent will be required from mothers before: 1) administering the household survey; and 2) delivering the information intervention. For each of three consent processes, an information form will be read and given to participants on the purpose of the study, the risks and benefits of the study, the broad content of the interview, the confidentiality of the data, the voluntary nature of the interview, the possibility of stopping the study or interview at any time without reason, and the contact details of the principal investigators. Consent from women indicated by a thumb print, with written confirmation by the enumerator of such consent being given, will be sought and must be given prior to the information intervention being delivered or the interview commencing.

## Data Management

An important ethical risk of the study pertains to breaches of confidentiality. The study will make every effort to minimise the risk of breaches of confidentiality, particularly in relation to data management and the linking of datasets. The research intends to link data from different sources. The linking of data with geographical identifiers elevates the importance of maintaining confidentiality.

A number of steps will be taken in terms of management of the data. First, data using the various data collection tools will be entered by enumerators at the time of interview and will be linked only by the PIs for the purposes of random assignment and analysis. In this way, misuse or breach of confidentiality at the data entry level will be reduced by a great extent. Second, data will be stored electronically (no paper questionnaires are to be used) in London (at LSHTM) and Delhi (at Sambodhi) and will only be accessed by the PIs and other members of the research team. No other persons will have access to the securely kept data.

Third, the datasets will contain no information that would allow identification of any individual woman or household. They will contain no information on names or GPS information. The village cluster will be coded such that it is not possible to know the name of the village from the datasets. GPS information on households will be collected using a separate data collection form, entered into digital format separately and the digital format of the data will be stored in its own data file. Datasets will not be linked to the GPS information dataset, except by the PIs at the time of analysis. The variables containing the GPS information will otherwise be scrambled such there is an uncertainty in the location of observation of at least 10 kilometres.

Fourth, as is common practice, data will be reported in aggregate format only (eg. means, subgroup means, percentages, regression outputs) such that no individual is identified. Finally, at the end of the project the data will be made available to researchers under conditions of restricted access. The data can only be used for research or teaching purposes. Access the data will be granted by the PIs on an individual basis in response to requests made using a form. The data will not contain any identifiers or names that would allow identification of an individual. The platform to make the data available to researchers will be the LSHTM data repository.

# Appendix

## Updates to the original study protocol

A number of changes were made to the original study protocol (dated 3rd December 2014) before the baseline household survey and the delivery of the information intervention. These changes are reflected in both this version of the study protocol and the online trial registration for the study. The changes and the justification for the changes were as follows:

- Eligible mothers were randomly assigned in a ratio of 1:1:1 to one of three study arms using simple randomisation. In the original study protocol it stated that randomisation would be stratified according to distance of the residence to the nearest public health facility. We did not collect data on distance to the nearest public health facility because we felt such information would be unreliable.
- Potentially eligible participants were identified through two channels: a household survey conducted by the research team nine months prior to the study and a list of mothers who had given birth in the past year provided by the community health worker (known as ASHAs) in each village. In the original study protocol it stated that all participants would be identified through the first channel only. After collecting data from the household survey conducted nine months prior to the start of the study, it became clear the sample sizes obtainable from this method would be insufficient. Hence, the second channel of identifying eligible participants was also used.
- One criteria for inclusion in the study was that the child should be aged 0-36 months. In the original study protocol the age range was 0-11 months. Revisions to the study protocol recognised that older children should be eligible because they can receive catch-up vaccinations for DPT.
- In the original study protocol we envisaged collecting data on general health care seeking behaviour of members in the participating households using a family health pictorial diary. This data collection method was dropped altogether.

## Deviations from the study protocol

There were deviations from the study protocol as follows:

- Before the baseline household survey and the delivery of the information intervention, the secondary outcome measuring the proportion of children fully vaccinated was re-defined to no longer include polio, as originally stated in the study protocol. We did not collect any information on polio vaccinations in the household surveys.
- Prior to the data analysis, we planned to analyse the following additional secondary outcomes: the proportion of children with measles vaccination, the proportion of children with BCG, the mother’s knowledge of any cause of tetanus and her knowledge of any prevention method.
- In the study protocol, it stated that we would conduct subgroup analyses with respect to: 1) index of the mother’s perception of the efficacy of tetanus vaccination; 2) gender of the child; 3) household wealth; 4) education level of the mother; and 5) distance to the nearest government facility. The last three subgroup analyses were not conducted because we did not collect data on household wealth, education or distance to the nearest government health facility.
- The original protocol stated that a logistic regression would be used to produce odd ratios of the effect of the information intervention. Since simple randomisation was used that involved no stratification, we resorted to basic statistics to show the absolute difference and the relative risk between groups, with their corresponding 95% confidence intervals.
- We conducted several analyses that were unplanned. We decided to do these analyses after we had completed the analysis of the pre-specified outcomes, hence they are exploratory. First, we compared the mean in our measure of perception of DPT vaccine efficacy between treatment and control for two subgroups of women, with baseline perception of efficacy above and below the 50% threshold, respectively. Second, we carried out a cost-effectiveness analysis.

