| Notes: Sources are the Census 2011 and the Annual Health Survey 2012-13. The MMR estimates apply to groups of districts within the state due to sample size limitations. | | | | | | | |

A substantial proportion of children do not receive the vaccines recommended by the Government of India (Table 2). Just under two-thirds of children receive three doses of DPT in the state. Coverage of DPT3 in the study districts is either around the state average or above, with modest variation between districts. Coverage of measles largely mirrors that of DPT3. A higher proportion of children receive the BCG vaccine, the first of the routine immunisations given at birth. Only half of all children in the state are fully immunised against the six main vaccine preventable diseases implying that there are important barriers to uptake.

Table 2. Immunisation coverage for children aged 12-23 months

| Indicator | Uttar Pradesh | Kannauj | Kanpur Nagar | Kanpur Dehat | Auraiya | Etawah | Fatehpur |
| --- | --- | --- | --- | --- | --- | --- | --- |
| Children 12-23 months received 3 doses of DPT | 63.2 | 59.1 | 72.4 | 72.4 | 59.5 | 69.2 | 65.5 |
| Children 12-23 months received measles vaccine | 65.8 | 61.2 | 75.1 | 79.7 | 60.2 | 75.7 | 70.7 |
| Children 12-23 months with immunization card | 71.7 | 66.0 | 92.4 | 92.0 | 80.3 | 92.1 | 88.2 |
| Children 12-23 months received BCG vaccine | 86.3 | 90.5 | 89.4 | 92.6 | 84.9 | 91.3 | 91.1 |
| Children 12-23 months received 3 doses of polio | 64.1 | 59.1 | 73.2 | 70.8 | 60.2 | 72.7 | 65.5 |
| Children 12-23 months fully immunized | 52.7 | 46.4 | 59.2 | 61.9 | 46.2 | 58.0 | 51.5 |
| Notes: Source is the Annual Health Survey 2012-13. | | | | | | | |

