## Participants and Inclusion Criteria

The criteria for inclusion in the study include: 1) mother with a child aged 0-36 months living in the same household; 2) child has not received three doses of DPT vaccine; 3) mother gives consent to participate in the study; and 4) mother intends to remain in the study area for at least six months. The criteria for exclusion in the study include: 1) child of mother is not aged 0-36 months; 2) child of mother is not living in the same household; 3) child has received three doses of DPT vaccine; 4) mother does not give consent to participate in the study; and 5) mother due to emigrate from the study area in the next year.

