### Initial and final household survey

A baseline survey of eligible women will capture information on: 1) the presence of a vaccination card; 2) whether the child has been vaccinated against tuberculosis, diphtheria, pertussis, tetanus, polio and measles, respectively; 3) the mother’s knowledge of tetanus symptoms, and 4) the mother’s perceptions of the efficacy of tetanus vaccination. The latter will be measured using an established technique in which women are asked to ascertain the likelihood of various events happening by placing beans in a cup. The endline survey will use a very similar tool nine months after the baseline survey.

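### The added BCG outcome (and, less so, measles) is cumulative coverage in all randomised children, so it barely responds to new uptake and a null would say little about carry-over

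*Protocol*

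**What the plan says.** Under Deviations from the study protocol, the appendix says "Prior to the data analysis, we planned to analyse the following additional secondary outcomes". The list includes "the proportion of children with measles vaccination, the proportion of children with BCG". No restriction to post-randomisation doses, or to children lacking the vaccine at entry, is given. The same section replaces the planned regression with simple absolute differences and relative risks between groups, and mentions no baseline adjustment.

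Under Participants and Inclusion Criteria, the only vaccine criterion is "child has not received three doses of DPT vaccine". The age range is 0-36 months.

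The Uttar Pradesh section states: "A higher proportion of children receive the BCG vaccine, the first of the routine immunisations given at birth". Its Table 2 gives coverage at 12-23 months for each study district.

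Under Initial and final household survey, the baseline interview records "whether the child has been vaccinated against tuberculosis, diphtheria, pertussis, tetanus, polio and measles, respectively". The appendix later withdraws polio from this list, but not tuberculosis or measles.

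**The concern.** The DPT3 criterion sets the primary outcome to zero at entry, so any child positive at nine months was vaccinated during follow-up. The fully vaccinated outcome is zero at entry for the same reason. Nothing does this for BCG or measles. A child with BCG at birth is a success in whichever arm it falls and cannot respond to the script, yet stays in numerator and denominator.

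If a share b already has the vaccine, the absolute difference shrinks by the factor (1 - b) and the relative risk moves towards 1. Readers will probably set the BCG and measles results beside DPT3 to judge whether information about one vaccine affects others. A difference near zero could then be taken as no carry-over, when the measure had little room to move.

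**Working it through.** **1. The plan's own figure.** Table 3, pooled information arms versus control, 10% control rate and a 7-point difference, gives 288/576. The usual two-proportion formula (two-sided 5%, 80% power, 2:1, pooled variance under the null, no continuity correction) gives 287.3, rounded up to 288. All the control-group sizes in that part of the table reproduce the same way. The Protocol describes about 7 points as detectable with its available sample, so 288/576 is used below.

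**2. Who already has BCG or measles vaccine among children without DPT3?** Table 2 covers all children aged 12-23 months, so it must be converted to children without DPT3.

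- Lower bound, if every DPT3 child also has vaccine V: (V - DPT3) / (100 - DPT3).
- Upper bound for measles, since fully immunised children have both vaccines: (measles - fully immunised) / (100 - DPT3).

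For BCG, statewide: (86.3 - 63.2) / (100 - 63.2) = 23.1 / 36.8 = 62.8%.

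| Area | DPT3 | BCG | Measles | Fully immunised | BCG without DPT3, at least | Measles without DPT3, range |
|---|---|---|---|---|---|---|
| State | 63.2 | 86.3 | 65.8 | 52.7 | 62.8% | 7.1-35.6% |
| Kannauj | 59.1 | 90.5 | 61.2 | 46.4 | 76.8% | 5.1-36.2% |
| Kanpur Nagar | 72.4 | 89.4 | 75.1 | 59.2 | 61.6% | 9.8-57.6% |
| Kanpur Dehat | 72.4 | 92.6 | 79.7 | 61.9 | 73.2% | 26.4-64.5% |
| Auraiya | 59.5 | 84.9 | 60.2 | 46.2 | 62.7% | 1.7-34.6% |
| Etawah | 69.2 | 91.3 | 75.7 | 58.0 | 71.8% | 21.1-57.5% |
| Fatehpur | 65.5 | 91.1 | 70.7 | 51.5 | 74.2% | 15.1-55.7% |

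A BCG majority holds in every district. A measles majority is ruled out for the state, Kannauj and Auraiya, and is possible but not shown in the other four.

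**3. Effect on the comparison.** Assumption: new uptake among children not yet vaccinated is 10% (control) versus 17% (information). This is the DPT3 planning case, borrowed because the Protocol gives none for BCG or measles. Endline coverage is p = b + (1 - b) x new uptake. Power is Φ((Δ - 1.96 s0) / s1), where s0 and s1 are the standard errors under the null (pooled) and the alternative.

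For b = 62%:
- p = 0.62 + 0.38 x 0.10 = 0.658 versus 0.62 + 0.38 x 0.17 = 0.685, so Δ = 0.0266.
- s0 = 0.0338 and s1 = 0.0340, so power = Φ(-1.17) = 12%.

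| Share already vaccinated | Difference, all children | Relative risk | Power, all children | Power, unvaccinated at baseline only |
|---|---|---|---|---|
| 0% (as for DPT3) | 7.0 points | 1.70 | 80% | 80% |
| 36% (state upper bound, measles) | 4.5 points | 1.11 | 24% | 60% |
| 62% (low BCG bound) | 2.7 points | 1.04 | 12% | 39% |
| 77% (high BCG bound) | 1.6 points | 1.02 | 8% | 24% |

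The restricted analysis uses 288(1 - b) and 576(1 - b) children: about 109/219 at 62% and 66/132 at 77%. With an unpooled variance the restricted BCG figures become 45% and 30%, so the range is 39-45% and 24-30%.

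**4. Validity.** With no effect, 288/576 children and b at 63% or 90%, simulated type I error was about 5.0%. Prior vaccination costs sensitivity, not validity.

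**The case against.** The strongest reply is that nothing is biased. Vaccination before randomisation is balanced in expectation, the all-children difference correctly estimates the effect on coverage in everyone randomised, and type I error is kept. If most children have BCG, information can raise its coverage only slightly, and a small difference reports that faithfully. All of this stands. A reader might infer that the definition manufactures a false null; the documents do not support that. A true null is also possible, since the script concerns DPT and chiefly tetanus.

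A reader might also infer that most children already have both vaccines, or that 84.9% to 92.6% have BCG at entry. Those Table 2 rates describe all children aged 12-23 months, whereas the trial selects children without DPT3. For that group the table guarantees only 61.6% to 76.8% for BCG, and it caps measles at 64.5% in the highest district.

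The Protocol gives no reason for adding these outcomes and nowhere says they test carry-over. BCG and measles are components of the fully vaccinated outcome, and reporting components as coverage is ordinary. An analysis plan that is not shown may also deal with baseline status. These points limit the weight of the concern. They do not remove it: the outcomes as worded, with the unadjusted statistics the appendix describes, leave baseline vaccine status unused.

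Finally, restriction does not make BCG well powered. That is true, but it improves power in every scenario above and asks the question of children who can still respond.

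**Conclusion.** The point holds for BCG and more weakly for measles. The added BCG outcome is a valid measure of coverage and a poor measure of new uptake. A behavioural effect that the trial would detect with 80% power for DPT3 would be detected with about 8% to 12% power for BCG. A null would therefore be uninformative about carry-over.

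For measles the size cannot be fixed. The share already vaccinated is bounded at 7% to 36% for the state, with wider bounds in some districts. At 36%, power would be 24% for all children against 60% among those unvaccinated at baseline.

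The figures rest on the borrowed uptake of 10% versus 17%, on 288/576 children, and on Table 2 bounds for ages 12-23 months. The trial enrols ages 0-36 months, partly from lists of births in the past year, and its age mix is not given. The primary outcome and the fully vaccinated outcome are unaffected.

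**What to change.** - Define the BCG and measles outcomes as new vaccination by nine months among children recorded without that vaccine at baseline, or keep all children and adjust for baseline status. Baseline status precedes randomisation, so the restricted comparison remains a randomised one.
- Report all-children coverage at nine months beside baseline coverage, by arm, as description.
- State that a null result for BCG does not show absence of carry-over.
- If the data have already been analysed, as the appendix's past-tense account suggests, label this analysis post hoc.

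The cost is a few sentences and one further analysis, with no new data: the baseline survey is set to record both vaccines. The denominator falls and the absolute interval widens. In the scenarios above, the 95% half-width goes from about 6.7 to 7.5 points at 62% already vaccinated (1.96 x 0.0340 and 1.96 x 0.0383), and from about 5.7 to 9.6 points at 77% (1.96 x 0.0290 and 1.96 x 0.0492). Power recovers only in part, to about 24% to 45% for BCG.

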### Anticipated effects

A health information intervention could theoretically have one of three effects. If individuals lack accurate information and their priors are lower than the true efficacy of healthcare, then giving information could motivate households to increase uptake of healthcare. On other hand, if individuals hold perceptions that are more optimistic than the true efficacy of healthcare, providing information could lead to reduced demand. Finally, providing information will likely have no effect if families already hold accurate beliefs about the efficacy of healthcare, heavily discount the future, or face supply-side constraints that make it difficult to increase uptake of healthcare. Peer effects – the effect on families socially connected to recipients of the intervention – can be expected primarily through further dissemination of the information between families although other channels are also possible ([Dupas, 2014](#_ENREF_5), [Kremer and Miguel, 2007](#_ENREF_12)).

How decisions are framed can have a powerful influence on choices. In particular, people tend to be sensitive to the gains and losses associated with the outcome of a decision because of loss aversion. This refers to people’s tendency to prefer avoiding losses to acquiring gains. A large literature on reference dependent preferences demonstrates behaviour consistent with a notion of loss aversion ([Kahneman and Tversky, 1979](#_ENREF_11), [Tversky and Kahneman, 1991](#_ENREF_29)). Lab experiments have consistently demonstrated that subjects are more responsive to protocols framed as losses than to protocols framed as gains and there is a growing body of field experiments testing the effect of the loss frame in marketing messages on product demand ([Bertrand et al., 2010](#_ENREF_2)). In light of the literature, it is anticipated that the information script framed as a loss (incurred by not vaccinating the child) will increase uptake of DPT immunisation more than the information script framed as a gain (incurred by vaccinating the child).

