# Study Objectives

The study will test the extent to which an intervention designed to improve household perceptions of the efficacy of preventative care increases uptake of the service in Uttar Pradesh. It will use the DPT vaccine as a case study to examine this question. The specific objectives of the study are:

1. To examine whether providing accurate information regarding the effectiveness of DPT vaccine affects demand for and uptake of the service
2. To examine whether negative framing relative to positive framing enhances the effect of the information on service uptake
3. To examine whether the effect of information is greater amongst those who initially have lower perceptions of the efficacy of DPT vaccine

The study involves a randomised field experiment to test whether information given to households on the actual effectiveness of healthcare can shift perceptions thereby increasing demand and uptake. It would only be ethical to attempt to provide households with information on health interventions for which there is rigorous evidence on efficacy. The general principle will thus be tested using an information intervention specific to the DPT vaccine for which there is strong and widely accepted evidence on efficacy.

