## Analysis

The primary analysis will compare the proportion of children with three doses of DPT in the two treatment groups pooled together against the control group. A logistic regression with a dummy variable representing the two treatment groups combined will produce risk ratios with 95% confidence intervals adjusted for the distance stratifying variable (included as two dummy variables), with the control group as the omitted reference category. Fully adjusted risk ratios will also be generated with the inclusion of baseline characteristics. Secondary outcomes will be analysed in a similar manner, but using OLS in the case of continuous outcomes.

Several additional analyses will be conducted. First, an analysis to identify the effects of the two variants of the intervention will be conducted in a treatment group analysis. Each of the three groups will be compared against each other. The comparison between the two information groups will identify whether framing matters. Second, an analysis of information spillovers will be conducted by exploiting random variation in the geographical density of households assigned the treatment groups ([Dupas, 2014](#_ENREF_5), [Kremer and Miguel, 2007](#_ENREF_12), [Miguel and Kremer, 2004](#_ENREF_19)). Information on the geographical coordinates of households will be used to generate a variable that indicates for each household the share of other households within a given radius who received the information intervention. The presence of information spillovers is examined by the inclusion of this density variable. The sensitivity of the results to different radii will be explored (ie. 250 metres, 500 metres, 750 metres). Third, differences in the primary endpoint across specified subgroups will be assessed by adding a treatment-by-subgroup interaction terms to the binary regression models. This will be done separately for the following subgroups measured at baseline: 1) index of the mother’s perception of the efficacy of tetanus vaccination; 2) gender of the child; 3) household wealth; 4) education level of the mother; and 5) distance to the nearest government facility. In the analysis of secondary outcomes, OLS will be used in the case of continuous outcomes.

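### The exploratory analysis by baseline perception cuts a graded measure at an unexplained 50% and compares arms within each half, so it cannot by itself show that the effect differs

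*Protocol*

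**What the plan says.** Four places in the Protocol bear on this point.

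- **Study Objectives, objective 3:** "To examine whether the effect of information is greater amongst those who initially have lower perceptions of the efficacy of DPT vaccine".
- **Initial and final household survey:** the modifier is graded, because "women are asked to ascertain the likelihood of various events happening by placing beans in a cup". The number of beans, the distribution and the standard deviation are not given.
- **Analysis:** the planned test is that "differences in the primary endpoint across specified subgroups will be assessed by adding a treatment-by-subgroup interaction terms to the binary regression models". The mother's perception index heads the list of subgroups, beside child gender and three others. No cut-point is stated for it.
- **Appendix, Deviations from the study protocol:** among analyses declared unplanned and exploratory, the mean of the perception measure is compared between arms in "two subgroups of women, with baseline perception of efficacy above and below the 50% threshold, respectively". The outcome is perception, a secondary outcome, and not DPT uptake. No rationale for 50% and no interaction estimate is given. The same section drops three planned subgroup analyses (wealth, education, distance). The perception index is not among them.

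**The concern.** The question behind both analyses is graded: does the effect grow as initial perception falls? The exploratory analysis answers a coarser one, at a dividing point the protocol does not support. Under Anticipated effects, a rise in uptake is expected "If individuals lack accurate information and their priors are lower than the true efficacy of healthcare", and a fall is possible where priors are too optimistic. The dividing point in that argument is true efficacy. Nothing in the protocol puts it at 50%; the description of the information scripts carries only placeholder letters for the efficacy figures. A mother at 55% and one at 95% share a group, although the first may be well below the truth and the second at or above it.

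Two things are at stake. The cut makes real effect modification harder to see. And where arms are compared separately in each half, a reader may take a clear result in one half and an unclear one in the other as evidence of a difference. The cut was also chosen after the pre-specified outcomes had been analysed, so an unexplained threshold is open to the suspicion that the data suggested it.

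**Working it through.** **The protocol's own figure.** Table 3 sizes main effects only; no power is given for any subgroup or interaction analysis. For the pooled comparison (control 10%, treated 17%, two treated per control, two-sided 5%, 80% power):

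- average proportion = (0.10 + 2 × 0.17)/3 = 0.1467
- control n = [1.960 × √(1.5 × 0.1467 × 0.8533) + 0.842 × √(0.10 × 0.90 + 0.17 × 0.83/2)]² / 0.07² = (0.849 + 0.337)² / 0.0049 ≈ 287.3, rounded up to 288

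This matches the stated 288/576. It fixes the 5% level and 80% power used below, and says nothing about the modifier.

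**Information lost by the cut.** Let q be the share of women below 50%. The protocol does not give q, so a range is shown. If the effect is linear in the index, the share of information kept is the squared correlation between the index and its two-group version:

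- normal index: φ(c)² / [q(1 − q)], with c = Φ⁻¹(q)
- uniform index: 3q(1 − q)

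If the graded interaction test has 80% power, the cut version has power Φ(2.802 × √kept − 1.960), where 2.802 = 1.960 + 0.842. Examples:

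- uniform, q = 0.5: kept = 3 × 0.25 = 0.75; Φ(2.802 × 0.866 − 1.960) = Φ(0.466) = 0.68
- uniform, q = 0.1: kept = 3 × 0.09 = 0.27; Φ(2.802 × 0.520 − 1.960) = Φ(−0.504) = 0.31

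**Reading two separate comparisons.** Suppose the true effect is the same in both halves and the whole sample has 80% power. A half holding share s of the women has power Φ(2.802 × √s − 1.960). With powers a and b, exactly one half is significant with probability a(1 − b) + b(1 − a). At q = 0.5, a = b = 0.508, which gives 0.50. At q = 0.3, the powers are 0.335 and 0.650, which gives 0.55.

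| q | Normal: kept | Normal: power | Uniform: kept | Uniform: power | Exactly one half significant, equal effects |
|---|---|---|---|---|---|
| 0.5 | 64% | 61% | 75% | 68% | 50% |
| 0.3 | 58% | 57% | 63% | 60% | 55% |
| 0.2 | 49% | 50% | 48% | 49% | 61% |
| 0.1 | 34% | 37% | 27% | 31% | not computed |

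The loss is present in every row and is largest when few women fall below the cut. With identical effects, the two halves disagree on significance in half or more of trials over the range computed.

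**The case against.** The strongest reply is that this is a labelled exploratory display, reported in the past tense, with perception as its outcome. The sentence mentions no significance test and draws no conclusion about effect modification. That stands, and it is the main reason for low severity.

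A reader might infer that the trial never tests whether the effect differs by initial perception, or that the 50% split is the test of objective 3. The protocol does not support either reading. The Analysis section plans an interaction on the primary endpoint with the perception index as modifier, and the list of dropped subgroup analyses leaves it in place. The Deviations section also says that regression for the main effect gave way to basic statistics, without saying what became of the interaction model. That silence does not show that the interaction was abandoned. Nor can a loss of power on DPT uptake be charged to the 50% cut, because no section describes a DPT interaction using it.

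It can also be said that coding the index is a matter for a statistical analysis plan, and that the Analysis section is compatible with an uncut term. That is fair: listing a graded index as a subgroup beside gender leaves the coding open and is not an error. What the reply does not remove is that the one cut the protocol states has no reason given and comes with no estimate of the difference in effect.

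**Conclusion.** The point holds for the exploratory comparison of mean perception. As described, it splits a graded modifier at 50% without justification, and its two treatment-control contrasts cannot by themselves show that the effect differs between women with low and high initial perception. The cost of the split is illustrative: 27–75% of the modifier information kept, and 80% power reduced to about 31–68%. Those figures assume an effect linear in the index, a normal or uniform distribution, and 10–50% of women below the cut; none of these is in the protocol. If the effect truly stepped at 50%, the cut would not carry this loss, but the protocol gives no ground for expecting a step there. The planned DPT interaction is not at fault; it would only benefit from saying that the index enters uncut. This is a low-severity, inexpensive improvement.

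**What to change.** - **Deviations from the study protocol:** fit a treatment-by-baseline-perception interaction with mean perception as outcome and the baseline measure uncut. Report the coefficient with its 95% confidence interval. Keep the 50% split only as a descriptive display, and rest no statement about effect modification on it.
- **Analysis:** state that the perception index enters the planned DPT interaction uncut, with a quadratic or spline term as a sensitivity check.

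The cost is a few lines of wording and regressions on data already collected. The downside is small: a single linear term is an assumption, which the sensitivity check addresses, and a slope is slightly harder to present than two subgroup means.
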